### Participants and Sample Size Calculation

The sample size was calculated according to the Asymptotic normal method (40). Obtaining a power of 80% and taking a *p*-value of 5%, the number of participants expected to have in the study is *n* = 81, which is similar to other studies in the field (30, 31). The formula used for calculating the sample size (40, 41) is:

$$\begin{array}{l} n=\frac{{\left[Z\left(\alpha /2\right)\sqrt{\left(2P\left(1-P\right)\right)}+Z\left(\beta \right)\sqrt{\left(P1\left(1-P1\right)+P2\left(1-P2\right)\right)}\right]}^{2}}{{\left(P1-P2\right)}^{2}} \end{array}$$

Where *P* = 0.5^*^(P1 + P2), Power = 1-β and Z(α/2) and Z(β) are taken from the z table. For this particular case, P1 corresponds to the expected outcome in the control group and P2 the expected outcome in the intervention group. The primary outcome measure is the Visual Analog Scale (VAS) that consists of 10 points (100%) and when considering a clinically significant decrease and difference of 2 points (20%), these values would correspond to 80 and 60%, respectively (P1: 80 and P2: 60). Replacing these values in the above equation, the sample size is:

$$\begin{array}{l} n=\frac{{\left[1.96\sqrt{\left((2.07)*(1.07)\right)}+0.842\sqrt{\left(0.8*(1-0.8)+0.6*(1-0.6)\right)}\right]}^{2}}{{\left(0.2\right)}^{2}}\\ \;=81.25\;\approx \;81 \end{array}$$

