### Primary Outcome Measure

Primary outcome measure is a Visual Analog Scale (VAS) of 0-10. 0 indicates a state without any pain and 10 indicates the most severe pain possible. Each number from 0 to 10 is distributed in a line 1 cm apart and the patient can mark the intensity of pain felt at the time of filling out the VAS. The VAS will be applied at baseline, and every time before, after, and at 3 h post-each intervention. Period of data collection: maximum 2 weeks from the point of study entry.

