### Secondary Outcome Measures

The Colombian version of the Hospital Anxiety and Depression Scale (HADS) (45) will be applied to measure anxiety and depression levels of the participants. The HADS consists of a 7-item anxiety subscale and a 7-item depression subscale rated on a four-point Likert scale. The higher the total points on each scale, the greater the risk of a depressive or anxiety disorder, with a maximum score of 21 for each subscale. The HADS scale will be applied at baseline, after the third, and after the last intervention. Period of data collection: maximum 2 weeks from the point of study entry.Vital signs (heart rate, respiratory rate, oxygen saturation, blood pressure) will be measured via hospital monitors before the intervention, after the intervention, and at 3 h post-intervention. Period of data collection: maximum 2 weeks from the point of study entry.The use of pain medication refers to the frequency and dose of additional analgesic medications requested by the patient during the study period (complementary or rescue doses). The total amount of dosage and frequency will be calculated by summing up individual records. Period of data collection: maximum 2 weeks from the point of study entry.

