### Data Management and Statistical Analysis

Data collection and storing will be done manually and later transcribed to an electronic database. The accuracy of data transcription will be checked by randomly selecting 20% of the participants for whom a double-data entry procedure will be implemented as a means for control of potential errors while transcribing the results from the paper questionnaires to the electronic database. The original questionnaires will be stored in a locked shelf inside the ICU and digital data storing and processing follows the institutional guidelines for data security, including a password protected laptop, encrypted files, and using secure methods of file transfers.

Data analysis will be performed by analysts blinded to the randomization outcomes and based on an intention-to-treat analysis (ITT) (49). Basic socio-demographic and medical data will be analyzed using descriptive statistics and compared between the two groups to detect any differences in the population. For the differences of the main outcome measure (pain) and the secondary outcome measures (anxiety and depression, vital signs, use of analgesics), ANOVA (analysis of variance), the *p*-value test, and the Mann-Whitney *U*-test will be performed. When analyzing the data, a univariate analysis will be carried out in which the frequency (absolute and relative), percentages and confidence intervals of the different qualitative variables will be established. Subsequently, the association between the different variables will be evaluated through the Chi-square χ^2^ test. Additionally, the Shapiro Wilk test will be used to determine the distribution of the quantitative variables. Once this result is obtained, we will seek to determine the mean, standard deviation, central tendency, and dispersion for the variables of normal distribution, while the median and interquartile range will be sought for those of non-normal distribution. These variables will be evaluated using the Student's *t*-test or the Mann-Whitney *U*-test according to the distribution. The results will be considered statistically significant when observing a value of *p* < 0.05 (5%). Finally, a multivariate analysis will be carried out where logistic regression will be used to determine the contribution of each of the different quantitative variables in terms of the observed results.

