## Potential Limitations

We have also identified several potential limitations of this study protocol. First, background pain is influenced by many different factors, such as the medical condition of the patient, the number of procedures, mental health, and social support, among others. This means that a diversity of factors can potentially affect the pain perception of patients. This might be different during procedural pain, in which a more direct relationship between the procedure and the pain experience exists and thus immediate effects of music interventions might be observed more consistently. However, as mentioned at the end of the previous section, background pain in burn patients is an under-investigated topic and may be highly relevant for long-term well-being and health. While an accumulative effect of the MAR intervention over time may lead to an improved relaxation response and coping mechanisms and thus to reduced pain levels and improved mental health, little is known about the ideal dosage or frequency of music interventions. Formal moderator/mediator analyses in the fields of music therapy and music medicine may help in addressing such issues and are clearly needed (71–73).

Another limitation might be the broad inclusion criteria, which could affect the statistical power of the study. This was chosen since recruitment during COVID pandemic might be slower than expected, as ICU beds usually are prioritized for COVID patients during each infection peak. Thus, to keep recruitment within a feasible time frame, this study does not focus on a specific patient group within the burn population.

And third, other outcome measures including EEG, EMG, and ECG measurements are an exploratory feature of this study and due to the small sample size, the results can thus not be generalized. However, we consider them as important first steps in materializing the need for describing potential neurophysiological pathways and mechanisms of live MAR interventions based on the principles of entrainment.

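### Baseline VAS and HADS are collected, but the named group comparisons use no covariate, so the trial gives up precision it could have at almost no cost

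*Protocol article*

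**What the plan says.** The Data Management and Statistical Analysis section of the protocol article names the tests: "For the differences of the main outcome measure (pain) and the secondary outcome measures (anxiety and depression, vital signs, use of analgesics), ANOVA", followed by a p-value test and the Mann-Whitney U-test. Further on it says that quantitative variables go to Student's t or Mann-Whitney, depending on their distribution. No covariate appears in any of these. The only multivariable model is a closing logistic regression on the quantitative variables. It has no stated treatment term, baseline score or binary outcome, so it yields no adjusted treatment effect on VAS or HADS.

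Baseline scores are nevertheless collected. Under Primary Outcome Measure: "The VAS will be applied at baseline", and then before, after and 3 hours after each session. Table 1 marks the baseline VAS in the enrolment column, ahead of allocation. Under Secondary Outcome Measures: "The HADS scale will be applied at baseline, after the third, and after the last intervention". In the text of Table 1 available to us the baseline HADS cell is blank, which may be a conversion fault.

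Potential Limitations lists "the broad inclusion criteria, which could affect the statistical power of the study" as a concern. It also says that background pain depends on many factors and that an effect of MAR may accumulate over time.

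**The concern.** The section commits to particular tests, and the t-test and Mann-Whitney test cannot take a covariate. The objection is therefore to the choice made and not to a detail left for the analysis plan.

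The protocol worries that a mixed population will cost it power. Part of that spread between patients is already visible in the enrolment score, and adjusting for it is the direct remedy. With about 40 patients per arm and broad eligibility, some chance imbalance in starting pain is plausible. An unadjusted estimate carries that imbalance in full. The tests allow for it through a larger standard error.

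The word for differences in the analysis sentence could instead mean change scores. That uses a prior value, but it is not the efficient way to do so. If the change is taken within each session, the score before sessions 2 to 6 follows earlier MAR sessions. The comparison then measures only the immediate effect and subtracts whatever has carried over.

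**Working it through.** **The plan's own figure.** The sample size section uses the two-proportion formula with P1 = 0.80, P2 = 0.60, P = 0.70, two-sided 5% and 80% power:

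n = [1.96 × √(2 × 0.7 × 0.3) + 0.842 × √(0.16 + 0.24)]² / 0.2² = 81.25.

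This reproduces the stated result, but the formula returns patients per arm. The abstract uses 81 as the total, and the eight participants given as about 20% of the intervention arm agree with about 40 per arm. At 40.5 per arm, power on the protocol's own proportions is about 50%. That is a separate fault, but it shows that the trial has no precision to waste.

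**Inputs for the adjustment.**
- From the article: 81 patients at 1:1 (taken as 40 and 41), two-sided 5%, a 2-point difference on the 0-10 VAS.
- Assumed, because the article gives neither: SD of the VAS outcome 2.0 to 4.0 points; correlation r between enrolment and outcome score 0.3 to 0.7. The SD is taken as equal at both times, and no dropout is applied.

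**Variance relative to the unadjusted post score.** ANCOVA: 1 − r². Change from enrolment: 2(1 − r).

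| r | ANCOVA | Change score | ANCOVA / change | 81 patients count as 81/(1 − r²) |
|---|---|---|---|---|
| 0.3 | 0.91 | 1.40 | 0.65 | 89 |
| 0.5 | 0.75 | 1.00 | 0.75 | 108 |
| 0.7 | 0.51 | 0.60 | 0.85 | 159 |

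The ratio (1 − r²) / [2(1 − r)] equals (1 + r)/2, which never exceeds 1. ANCOVA is therefore at least as efficient as the change score at every correlation.

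**Power for 2 points (t-test, 40 against 41).** The standard error is SD × √(1/40 + 1/41), multiplied by √(1 − r²) for ANCOVA. Example at SD 3.5: the standard error is 0.778 and 2/0.778 = 2.57, giving 71.9%. With r = 0.5 the standard error is 0.778 × √0.75 = 0.674 and 2/0.674 = 2.97, giving 83.5%.

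| SD | Unadjusted | r = 0.3 | r = 0.5 | r = 0.7 |
|---|---|---|---|---|
| 2.0 | 99.4% | 99.7% | 99.9% | >99.9% |
| 2.5 | 94.5% | 96.1% | 98.4% | 99.9% |
| 3.0 | 84.2% | 87.4% | 92.8% | 98.6% |
| 3.5 | 71.9% | 75.9% | 83.5% | 94.5% |
| 4.0 | 60.4% | 64.4% | 72.8% | 87.5% |

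The adjusted columns already charge one degree of freedom for the covariate (78 instead of 79).

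A change-from-enrolment analysis at SD 3.5 has 57.4, 71.9 and 90.6% power at the same three correlations. At r = 0.3 it is worse than ignoring baseline altogether.

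**Within-session change, illustration only.** Suppose each session lowers pain by 1 point and half of the reduction present persists to the next session. The differences from control after sessions 1 to 6 are 1, 1.5, 1.75, 1.875, 1.9375 and 1.96875, with mean 1.67. The mean within-session change is 1.00. Both parameters are invented. The example shows the direction of the discrepancy, not its size.

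**The case against.** The strongest reply is that nothing here is invalid. Randomisation protects the unadjusted tests, and chance imbalance is already reflected in the standard error and p-value. That stands. A reader might infer that the planned comparison is biased, and the documents do not support this.

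Second, the analysis section is a loose list, and its wording could cover change scores or a repeated-measures ANOVA. So it is not certain that the post score alone will be compared, and the unadjusted column above applies only to that reading. This stands as a limit on the figures. It does not remove the point, because ANCOVA does at least as well as the change score.

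Third, the size is soft. A uniform spread over the whole 0-10 scale has an SD of 10/√12 = 2.9, so 3.5 is wide. The Introduction describes background pain as often low or moderate and its ICU course as hard to predict, which does not point to a high correlation. A reader who takes the SD 3.5 row alone would infer a substantial gain. The documents do not support that row over the others.

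Fourth, a reader might infer that the protocol expects benefit to accumulate, so that a within-session change must understate the effect. Potential Limitations says only that an accumulative effect may occur, and that little is known about dosage. If the immediate effect is the question, the within-session change does answer it.

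Finally, the text shown establishes timing before allocation for VAS only. Vital signs have no listed value earlier than the one before the first session, which follows allocation. Analgesic use has no baseline. This point is therefore confined to VAS and HADS.

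**Conclusion.** The point holds as a loss of efficiency in the pain and HADS comparisons. The variance reduction of 9, 25 or 51% at correlations of 0.3, 0.5 or 0.7 is arithmetic; which correlation applies is unknown. The gain in power runs from under 1 percentage point at SD 2.0 to about 4 to 27 points at SD 4.0. The direction holds for any material correlation, the lost degree of freedom being negligible at this size.

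A reader might hope that adjustment rescues the sample size. It does not: 81 patients carry the information of about 162 only if the correlation is about 0.7 (the table gives 159), and nothing in the article supports that value. The change is worth making because it uses scores already planned for collection, and because an adjusted analysis is more convincing if it is fixed before the data are seen.

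**What to change.** In the Data Management and Statistical Analysis section, replace the unadjusted primary comparison with one of two models, named in advance:

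- ANCOVA on a single stated VAS outcome (time point or summary), with treatment and enrolment VAS; or
- a mixed model over the post-session VAS scores, with treatment and enrolment VAS.

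Use the enrolment VAS as the covariate, not each session's own score before MAR. Analyse the HADS anxiety and depression subscales in the same way, each with its own baseline score, and confirm in Table 1 that baseline HADS is taken before allocation. Report adjusted mean differences with 95% confidence intervals. Keep Mann-Whitney as a sensitivity analysis instead of a route chosen after a normality test.

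The cost is one degree of freedom per model and slightly more analysis work. No extra patients are needed, and no measurements beyond those the article already lists. The sample size statement must still be corrected separately.

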## Abstract

**Background:** Burn patients experience major physiological and psychological stressors during treatment and rehabilitation, including elevated levels of pain, anxiety, stress, or depression. Music interventions inclusive of music therapy (MT) have been shown to improve such symptoms, but rigorous clinical trials investigating specific music therapy methods in adult burn patients are scarce.

**Methods:** This is a single center Randomized Controlled Trial (RCT) protocol with two parallel arms. Participants are 81 adult burn patients admitted to the Intensive Care Unit (ICU) of the University Hospital Fundación Santa Fe de Bogotá in Colombia. The intervention consists of a Music Assisted Relaxation (MAR) protocol, a music therapy technique composed of entrained live music combined with a guided relaxation and/or the use of imagery. The effects of the MAR will be compared to a control group (treatment as usual) over a period of maximum 2 weeks or six interventions. The primary outcome measure is perceived background pain, as measured with a Visual Analog Scale (VAS) before and after each intervention. Secondary outcomes are anxiety and depression levels; vital signs; and the use of pain medication. Additionally, some patients in the intervention group will be invited to participate in electroencephalography, electromyography, and electrocardiography recordings during the MAR.

**Discussion:** This study protocol follows the SPIRIT guidelines for defining items of clinical trials and is the first study in Colombia to evaluate the effects of music therapy for adult burn patients. With this RCT it is hoped to gather new knowledge about the potential of music therapy to help critical care patients cope and recover from their injuries during the hospitalization in the ICU.

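### The protocol fixes no single primary comparison for a VAS read up to 18 times after baseline, so the type I error of the primary outcome is uncontrolled

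*Protocol article*

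**What the plan says.** **Readings.** The Primary Outcome Measure section states: "The VAS will be applied at baseline, and every time before, after, and at 3 h post-each intervention". The Intervention section allows three sessions a week, for at most two weeks or six sessions. The Abstract describes the primary outcome as perceived background pain "as measured with a Visual Analog Scale (VAS) before and after each intervention" and does not mention the 3 h reading. Table 1 marks the VAS at every post-allocation time point and at close-out.

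**Analysis.** Data Management and Statistical Analysis treats pain together with anxiety and depression, vital signs and analgesic use. For differences in all of these, "ANOVA (analysis of variance), the *p*-value test, and the Mann-Whitney *U*-test will be performed". Later in the same section, quantitative variables are to be screened with Shapiro-Wilk and then compared by Student's t-test "or the Mann-Whitney *U*-test according to the distribution". One threshold, p < 0.05, applies to every result. Analysis is to be by intention to treat, with blinded analysts. A closing logistic regression is meant to show how quantitative variables contribute to the results; it is not presented as the primary comparison.

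**Sample size.** The calculation rests on one two-sided 5% test of two proportions ("Obtaining a power of 80% and taking a *p*-value of 5%, the number of participants expected to have in the study is *n* = 81"). It turns a 2-point VAS difference into 80% against 60% and names no time point.

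**The concern.** A primary outcome is fixed only when the reader knows which measurement, at which time or summarised in which way, is compared between arms. Here a patient can contribute up to 18 post-baseline values, and nothing in the article reduces them to one comparison.

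The list of tests does not do so either. ANOVA *and* Mann-Whitney in one sentence conflicts with t-test *or* Mann-Whitney a few sentences later, and the p-value test is not a test. The section names no model that accounts for correlation between one patient's readings, copes with patients who have different numbers of sessions, or adjusts for the baseline VAS that is being collected.

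Unequal numbers of sessions are to be expected. The Intervention section reports that 42% of the hospital's burn ICU patients stay up to one week, which at three sessions a week is about three sessions. The trial's own share may be lower, because eligibility requires an estimated hospitalization above seven days. At stake is whether a p-value below 0.05 for pain could be read as a 5% result.

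**Working it through.** **Inputs from the protocol article**
- Sessions: at most 6 (Intervention). VAS readings per session: 3 (Primary Outcome Measure).
- Participants: 81 in total (Abstract), allocated 1:1, so about 40 per arm.
- Test level: two-sided 0.05, with Z(α/2) = 1.96 (Participants and Sample Size Calculation).

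**Assumption.** The article gives no within-patient correlation ρ. I use 0.3, 0.5 and 0.7, equal between all sessions.

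**1. The plan's own figure.** With P = 0.7:

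n = [1.96·√(2·0.7·0.3) + 0.842·√(0.8·0.2 + 0.6·0.4)]² / 0.2² = (1.270 + 0.533)² / 0.04 = 81.25.

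This reproduces the stated 81.25. The calculation assumes one test on one value per patient but does not say which value. The article states no overall error rate for multiple comparisons, so there is no such figure to reproduce.

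**2. Number of readings.** 3 × 6 = 18 after baseline. The first pre-session reading precedes any treatment, so at most 17 can reflect it.

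**3. If one summary per patient is tested.** One value per patient and one pre-specified test gives a type I error of about 5%.

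**4. If sessions are pooled as independent values.** With k sessions per patient, the design effect is DE = 1 + (k − 1)ρ, and the true type I error is 2·[1 − Φ(1.96/√DE)].

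| k | ρ | DE | 1.96/√DE | Type I error |
|---|---|---|---|---|
| 3 | 0.3 | 1.6 | 1.55 | 12% |
| 3 | 0.5 | 2.0 | 1.39 | 17% |
| 3 | 0.7 | 2.4 | 1.27 | 21% |
| 6 | 0.3 | 2.5 | 1.24 | 22% |
| 6 | 0.5 | 3.5 | 1.05 | 29% |
| 6 | 0.7 | 4.5 | 0.92 | 36% |

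**5. If the six after-session readings are tested separately and any significant one counts.** Independent tests would give 1 − 0.95⁶ = 26%. A null simulation (40 per arm, 10,000 runs) gave 24.1%, 20.6% and 16.8% for ρ = 0.3, 0.5 and 0.7. Smaller runs with 40 against 41 patients stayed within 17–25%. With three sessions, the range is about 11–14%.

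**6. Choice of test at one time point.**
- Claiming whichever of t-test and Mann-Whitney is significant gave 5.4–6.6% in simulations of normal, rounded 0–10 and skewed 0–10 data.
- Applying the Shapiro-Wilk rule itself gave 4.9–5.2%.
- With two arms, one-way ANOVA and the t-test are the same test.

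The open choice of readings drives any inflation; the choice of test does not.

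**The case against.** The strongest reply is that the article does not commit to any inflating procedure. It never says that each time point will be tested, that sessions will be pooled, or that any significant reading counts as success. One mean, change score or last value per patient would fit the t-test and Mann-Whitney exactly and would accommodate unequal numbers of sessions. The type of ANOVA is also left open and could be repeated-measures. This stands. A reader might infer that the false-positive rate is far above 5%, or that the team must either pool sessions or test many time points. The article supports neither inference; the percentages in steps 4 and 5 are conditional scenarios.

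It can also be said that the Abstract merely condenses the Primary Outcome Measure section. That is fair: measuring before and after does not exclude a 3 h reading, so the two are not a firm contradiction. A further inference, that intention to treat is breached because late sessions contain only patients still present, presupposes session-by-session tests, which are not stated.

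Finally, a statistical analysis plan may exist, and model details and missing-data handling are usually left to it. That excuses missing detail, but not this point. The time point or summary belongs to the definition of the primary outcome, and on analysis the article is not silent: it commits to a list that is inconsistent and includes a test that does not exist. Blinding the analysts limits choosing a result by favoured arm, but not choosing it by p-value.

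**Conclusion.** The point holds in this form: up to 18 post-baseline VAS readings, no single primary comparison, and an inconsistent list of tests at an unadjusted 0.05 with no stated method for correlation, unequal sessions or baseline VAS. The type I error for the primary outcome is therefore uncontrolled.

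Its actual size cannot be read from the article. It ranges from about 5% with one summary per patient to 36% with six sessions pooled as independent at ρ = 0.7. These values rest on the assumed equal correlation of 0.3–0.7 and on every patient having the stated number of sessions; lower correlation or fewer sessions makes pooling less harmful. The switch between t-test and Mann-Whitney is untidy but not a material source of error. Because this concerns the primary outcome, it should be settled before any unblinded analysis.

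**What to change.** Replace the list of tests for pain with one pre-specified primary analysis. One suitable choice:

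- **Model:** a linear mixed model of the post-session VAS at all scheduled session assessments in both arms, including the control group's matched assessment times.
- **Terms:** arm, session number and enrolment VAS as fixed effects, with a patient random intercept.
- **Primary test:** the arm effect averaged over sessions, as the single two-sided 5% test.
- **3 h VAS:** secondary, in a separate model of the same form.
- **Deletions:** remove the p-value test, and remove distribution-based test switching for the primary outcome.

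Other single contrasts are defensible, such as a 3 h reading or one summary per patient adjusted for enrolment VAS. What matters is that one is named in advance and respects the within-patient correlation.

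**Cost.** This changes analysis wording only and uses data already being collected. A result at a single session could no longer be claimed as primary. The model also relies on a missing-at-random assumption for patients who leave early, which should be stated.

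### A Shapiro-Wilk test on the trial's own data picks the summary and test for VAS pain, and the non-normal branch states no between-arm estimate to set against the 2-point difference the trial was planned on

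*Protocol article*

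**What the plan says.** All of the analysis rules are in the protocol article, Data Management and Statistical Analysis.

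- **Methods for pain.** One sentence names ANOVA, a p-value test and Mann-Whitney for pain and the secondary outcomes. It does not rank them.
- **Pre-test.** A few sentences later, "the Shapiro Wilk test will be used to determine the distribution of the quantitative variables". Variables judged normal are described by mean and SD, "while the median and interquartile range will be sought for those of non-normal distribution". Student's t-test or Mann-Whitney then follows according to that result. Pain is not exempted.
- **Confidence intervals.** They appear once, for categorical data: "percentages and confidence intervals of the different qualitative variables will be established".
- **Decision rule.** The only criterion given is p < 0.05.

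Participants and Sample Size Calculation rests on "a clinically significant decrease and difference of 2 points (20" per cent of the scale). The analysis section does not return to that figure.

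Primary Outcome Measure describes a 0-10 line with the numbers printed 1 cm apart. Pain is scored at baseline and before, after and 3 h after each session. The Introduction describes background pain as often moderate or low in intensity.

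**The concern.** The trial is planned around a difference in VAS points, yet the written rule can lead to a primary result that is not a difference in points. Mann-Whitney asks whether scores in one arm tend to be lower than in the other; its p-value is not a test of a mean difference of any given size. If that branch is taken, a non-significant result does not show whether a 2-point benefit has been ruled out, and a significant one does not show whether the benefit is near 2 points or well below it.

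The choice is also made from the data. The same outcome could be reported as means after one session and medians after the next, and pain could be handled differently from HADS or heart rate. The article does not say whether the pre-test is run on each arm or on both pooled, and the answer can depend on that. The separate mention of ANOVA adds a third candidate for the primary analysis.

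**Working it through.** **1. The plan's own figure.** With P1 = 0.80, P2 = 0.60, P = 0.70, two-sided 5% and 80% power:

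n = [1.96 × √(2 × 0.7 × 0.3) + 0.842 × √(0.8 × 0.2 + 0.6 × 0.4)]² / 0.2² = (1.270 + 0.533)² / 0.04 = 81.25.

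This reproduces the stated 81.25. The 2 points enter the formula as a difference between two proportions, so no SD of the VAS is given anywhere, and SDs below are assumptions. The Abstract uses 81 as the total and allocation is 1:1, so I take 40 and 41 per arm. Whether 81 should have been a per-arm number is a separate matter and not part of this point.

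**2. How often would Shapiro-Wilk reject?** Normal scores were simulated, with values outside 0-10 set to the end of the scale. Each setting had 2,000 data sets, and the pre-test was at 5%. The means and SDs are assumptions.

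| Scores | Mean | SD | One arm, n = 40 | Pooled, n = 81 |
|---|---|---|---|---|
| Whole numbers | 2 | 1.5-2.5 | 99-100% | 100% |
| Whole numbers | 3 | 1.5-2.5 | 59-78% | 100% |
| Whole numbers | 4-5 | 2-2.5 | 16-29% | 66-92% |
| Continuous | 2 | 1.5-2.5 | 31-95% | 78-100% |
| Continuous | 3 | 1.5-2.5 | 5-49% | 6-93% |
| Continuous | 4-5 | 1.5-2.5 | 3-9% | 4-29% |

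For whole-number scores with mean 4-5 and SD 1.5, the rates are 62-63% per arm and 100% pooled. For whole-number change scores (SD 2, correlation 0.6, means 3-5, 1,500 data sets), they are 39-49% at n = 40 and 91-98% at n = 81.

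The branch therefore depends on the pain level, the spread, how the mark is recorded and whether arms are pooled.

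**3. What would an interval deliver?** For an unadjusted mean difference with one value per patient and all 81 analysed:

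half-width = t(0.975; 79) × SD × √(1/40 + 1/41) = 1.990 × SD × 0.2222.

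| Assumed SD | 95% half-width (points) | Significant if observed benefit exceeds | Excludes 2 points if observed benefit is below |
|---|---|---|---|
| 2 | 0.88 | 0.88 | 2 − 0.88 = 1.12 |
| 2.5 | 1.11 | 1.11 | 2 − 1.11 = 0.89 |
| 3 | 1.33 | 1.33 | 2 − 1.33 = 0.67 |

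Two readings follow that a p-value alone hides:

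- At SD 2.5, an observed benefit of 0.5 points gives −0.61 to 1.61. It is not significant, but it excludes 2 points.
- At SD 2, an observed benefit of 1.0 point gives 0.12 to 1.88. It is significant, yet it also excludes 2 points.

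**The case against.** Four counter-arguments deserve weight.

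- **Intervals are not forbidden.** The text attaches confidence intervals to qualitative variables but does not say they are confined to them. The article condenses a fuller document, and an interval for the primary contrast is commonly left to the analysis plan. This stands: the missing interval alone is no finding. The gate, however, is a stated rule.
- **Some estimate is in points.** Medians are in VAS points, and on the normal branch the mean, SD and n give an interval by hand. This stands too. The gap is narrower: the non-normal branch states no between-arm contrast with an interval.
- **ANOVA is named for pain without any condition.** True, so a mean-based analysis is part of the plan. But it sits beside Mann-Whitney with no order of priority, and a second rule follows that chooses by distribution. It leaves open which result is primary.
- **The Mann-Whitney branch is not certain.** True. The article does not say that marks are recorded as whole numbers, and at mean 4-5 rejection per arm can be as low as 16-29% for whole numbers or 3-9% for continuous scores.

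A reader might infer that the pre-test is bound to push pain to medians, or that the trial will be unable to say whether 2 points is reached or excluded. The documents support neither. The data would allow a mean difference or a Hodges-Lehmann shift with a usefully narrow interval, and nothing prevents its being reported.

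**Conclusion.** The point holds as a fault of pre-specification that is cheap to put right. The article fixes a data-driven choice of summary and test for the primary outcome, names ANOVA and Mann-Whitney together without priority, and on one branch links no effect estimate to the 2-point difference on which the sample size rests. That branch is likely if scores are low or marked in whole numbers, which the printed scale and the expected pain level make plausible.

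The gain from changing it is real: half-widths of about 0.9 to 1.3 points are well below 2. They rest on assumed SDs of 2 to 3, 40 and 41 patients, one value per patient, no dropout and no baseline adjustment. Dropout would widen them; adjustment for a correlated baseline would narrow them.

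**What to change.** Drop the Shapiro-Wilk gate for outcomes; it may stay for describing baseline data. Name one primary analysis of VAS pain:

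- the between-arm mean difference in VAS points with a 95% CI, using robust or bootstrap methods if scores are skewed;
- adjusted for the baseline VAS, which is already collected;
- at one named time point, or with a stated way of combining the repeated readings over up to six sessions.

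Read the interval against 2 points as well as p < 0.05. Keep Mann-Whitney as a sensitivity analysis, and say what role ANOVA has or remove it. Use the same form of estimate for HADS and vital signs, so that the measure does not change between outcomes.

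The cost is a short rewrite of the analysis section and a little more analysis work, with no new data. The time point or the way of combining sessions needs a real decision by the trial team. If scores prove very skewed, a mean-based analysis loses some efficiency compared with a rank test, which the sensitivity analysis would show.
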